### Ethical approval of the clinical trial

The research protocol was approved by the institutional ethics committees, including the University of Chile Faculty of Medicine (Approval certificate 060–2011; July 19, 2011), University of Chile Clinical Hospital (Approval certificate 53; July 27, 2011), San Borja Arriarán Clinical Hospital (Approval certificate 468–13; July 18, 2013), and also by the ethics committee of the National Fund for Scientific, Technological, and Innovation Development (FONDECYT) (Approval certificate G2-G3/590; May 24, 2012), the institution that approved the government grants for this clinical trial, all according to the Helsinki Declaration of the World Medical Association (2000).

### Trial management

Patients or their representatives will be asked to sign two copies of the informed consent. Patients will be given a copy of their consent form to keep for reference, and the other will be filed in the Investigator Site File on site. Data forms will be checked for completeness and merged into a master chart, which will be communicated to the study statistician. Patient confidentiality will be maintained at every stage.

Patients may withdraw from the trial or the trial treatment at any time without prejudice. Patients may be withdrawn from the study at the discretion of the local ethics committee for safety reasons. All adverse events and serious adverse events will be recorded during hospital stay and through patient communication while they are being subjected to ambulatory oral treatment. The study coordinator will conduct meetings with the study statistician on a regular basis, and the Chief Investigator will be made aware of all adverse events and serious adverse events as they happen.

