### Randomization and followup

Patients will be randomly allocated to one of the two groups. The allocation sequence will be centrally generated, stored, and assigned by using online randomization software (http://www.randomization.com) in random permuted blocks, each consisting of a box containing six treatment kits allocated in a placebo-to-vitamin treatment, 1:1 ratio for each participating center.

Random allocation is generated by intervention of the technician responsible for the treatment assignment to recruited patients, according to the sequence already established through the randomization method indicated previously. The reasons for losses and exclusions after randomization will be provided.

Neither participants, nor care providers, nor the investigators are aware of the treatment assignments. Adverse events, unintended effects and technical problems will be recorded.

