### Interventions

All patients will be asked to sign the informed consent before beginning the protocol. For those patients allocated to receive vitamin treatment, the intervention will be started as soon as the patient has signed the informed consent. The protocol will be started by administering an unique oral dose of vitamin E as α-tocopherol (800 IU) and an intravenous infusion of vitamin C as sodium ascorbate (320 m*M*) infused at a 10-ml/min flow rate during the initial hour and at 3 ml/min rate during the following 2 hours. Percutaneous coronary angioplasty will be performed about 30 minutes after initiating the vitamin C infusion. Oral doses of vitamin E (400 IU/day) and vitamin C (500 mg/12 hours) will be taken by the patients for 84 days after PCA.

For those patients allocated to receive placebo treatment, the 800-IU oral dose of vitamin E will be replaced for two vegetable oil capsules (400 mg each). The intravenous infusion of vitamin C will be replaced by an equal sodium chloride solution volume having the same osmolality as the vitamin C infusion administered to supplemented patients. The 400-IU oral doses of vitamin E will be replaced by vegetable oil (400 mg), and oral doses of vitamin C will be replaced with inert starch microgranules (500 mg). The pharmaceutical forms of vitamin C and E are indistinguishable from their respective placebos.

After the initial evaluation, patients will go to the catheterization laboratory. According to the standard protocol in AMI, an angiography will be performed to identify the infarct-related artery. The location and extent of AMI (number of arteries involved), percentage of stenosis, TIMI flow, type of stent, and so on, will be recorded. Immediately before coronary arteriography to confirm total occlusion of one coronary artery, a basal blood sample will be drawn from the antecubital vein. Three more blood samples will be obtained: immediately after successful reperfusion, at 6 to 8 hours after finishing the revascularization process and before hospital discharge.

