Infarct size, the primary endpoint of the study, will be measured with cardiac magnetic resonance (CMR) at 6 and 84 days (12 weeks) after PCA. Both determination and data obtained by these procedures will be evaluated by two independent individuals with the purpose of applying the concordance kappa index. Adherence to oral intake of vitamins C and E or placebo will be evaluated by telephonic contact effectuated weekly by the nurse responsible for the trial patient´s care.

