To our knowledge, no previous attempts have been made to use high doses of ascorbate to prevent or attenuate the myocardial damage caused by AMI. Pharmacokinetic studies on vitamin C in humans have shown that short-term infusion of high doses makes possible the reaching of peak concentrations even higher than 20 m*M*, but never being below 10 m*M* for at least 3 hours [84]. High doses of intravenous vitamin C have been reported to be remarkably safe, even when administered by infusions at a rate 3 times higher than that here proposed [85]. Nevertheless, patients having renal impairment or glucose 6-phosphate dehydrogenase deficiency, known possible complications of intravenous vitamin C, will be excluded from the present trial. However, a theoretic risk derived from high vitamin C levels is the development of kidney stones in unreported or first-time stone-forming patients [85]**.**

Regarding vitamin E possible adverse effects, current epidemiologic evidence (based on clinical trials that tested the effect of vitamin E supplementation in healthy participants and patients with various diseases) found that long-term supplementation with this nutrient shows a trend toward increasing slightly all-cause mortality (RR, 1.03; 95% CI, 1.00 to 1.05) independent of dose and exposition time [86]. However, the confidence interval is barely significant, because the lower interval is 1.00. In addition, as the Cochrane Meta-analysis explicitly excludes tertiary prevention trials, that is, randomized studies in which antioxidant supplements were used to treat a specific disease, such as trials involving patients with acute conditions (except nonmelanoma skin cancer), their conclusions are not applicable to our study.

Concerning the dosage, a previous meta-analysis reported that high-dosage supplementations (doses ≥400 IU/d) only increase all-cause mortality with expositions equal to or greater than 1 year [87]. Specifically in cardiovascular diseases, two recent meta-analysis that evaluate the efficacy of antioxidant supplements on these pathologies found no overall harmful effects in the analyzed endpoints [88,89], with the only exception of one controlled clinical trial [90]. However, those results are not consistent with the other related long-term large controlled clinical trials. In any case, that study supplemented the patients with twice our dose for more than a year, not being comparable in dose and timings with our study.

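### The post-discharge adverse-event window is worded by oral-treatment status rather than by calendar time to day 84, so follow-up of patients who stop early or never start capsules is left open

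*Protocol article*

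**What the plan says.** Two sentences in the protocol article deal with collecting adverse events.

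- **Trial management** covers all adverse and serious adverse events. They are to be "recorded during hospital stay and through patient communication while they are being subjected to ambulatory oral treatment".
- **Randomization and followup** is general: "Adverse events, unintended effects and technical problems will be recorded". It names no period.

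Four other provisions bear on how the first sentence works.

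- **Trial management** separates leaving treatment from leaving the trial: "Patients may withdraw from the trial or the trial treatment at any time without prejudice".
- **Interventions** fixes the planned oral phase: the capsules "will be taken by the patients for 84 days after PCA".
- **Interventions** sets the efficacy follow-up by calendar: infarct size "will be measured with cardiac magnetic resonance (CMR) at 6 and 84 days (12 weeks) after PCA".
- **Interventions** describes the outpatient contact by its purpose: "Adherence to oral intake of vitamins C and E or placebo will be evaluated by telephonic contact effectuated weekly".

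Statistical analyses compares adverse-event frequencies between arms by Fisher's exact test and mentions no allowance for time under observation.

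**The concern.** Efficacy follow-up is tied to the calendar, while safety follow-up after discharge is worded by whether the patient is on oral treatment. The protocol foresees patients who are off treatment and still in the trial. It does not say that event recording, or the weekly call, continues for them. A site that applied the Trial management sentence literally would bring such a patient back for the day-84 scan but record no event between the stop and that visit.

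A patient who receives the infusion and never begins capsules is in the same position from discharge onward. The design makes this possible. The infusion begins about 30 minutes before the angioplasty, whereas eligibility depends on TIMI flow before and after it (inclusion criterion 5 and exclusion criterion 5). Some patients could therefore be infused and then found ineligible. The article does not say whether they take capsules.

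The Discussion also names "a theoretic risk derived from high vitamin C levels is the development of kidney stones in unreported or first-time stone-forming patients". That exposure comes chiefly from the ascorbate infusion, which only the vitamin arm receives, and a stone could present after discharge.

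What is at stake is whether the arms are compared over the same period. Events that were never collected cannot be restored by an analysis plan.

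**Working it through.** There is no stated figure to reproduce, because the point concerns a collection rule. The check has two parts.

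**1. Does any provision close the gap?**

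| Provision | Period it fixes | Depends on treatment status? |
|---|---|---|
| Event recording, Trial management | Hospital stay, then the oral-treatment period | Yes, as worded |
| Event recording, Randomization and followup | None stated | Not stated |
| Weekly call, Interventions | None stated; purpose is adherence | Not stated |
| CMR, Interventions | Days 6 and 84 | No |

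Only the first row sets a window for events, and nothing expressly extends it to day 84 for a patient who has stopped.

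**2. How much could the literal reading matter?**

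All event and stopping rates here are assumptions; the article gives none. Its 10% allowance in Sample size is for patient loss, not for stopping treatment.

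Take constant hazards over 84 days, with stopping independent of events and collection ending at the stop. For a true event risk *p* and a proportion *s* stopped by day 84:

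- l = −ln(1 − p) and m = −ln(1 − s)
- recorded risk = l/(l + m) × [1 − (1 − p)(1 − s)]

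Worked case, with more stopping on vitamins:

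- Vitamins, p = 0.20, s = 0.20: l = m = 0.2231, so 0.5 × (1 − 0.80 × 0.80) = 0.1800.
- Placebo, p = 0.10, s = 0.05: l = 0.1054, m = 0.0513, so 0.6726 × (1 − 0.90 × 0.95) = 0.6726 × 0.145 = 0.0975.
- Recorded risk ratio = 0.1800/0.0975 = 1.85, against a true 2.00.

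The same formula gives (each pair is placebo / vitamins):

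| True risk | Stopped by day 84 | Recorded risk | Difference (points) | Risk ratio |
|---|---|---|---|---|
| 10% / 20% | 0 / 0 | 10.00% / 20.00% | 10.00 | 2.00 |
| 10% / 20% | 10% / 10% | 9.50% / 19.02% | 9.52 | 2.00 |
| 10% / 20% | 20% / 20% | 8.98% / 18.00% | 9.02 | 2.00 |
| 10% / 20% | 5% / 20% | 9.75% / 18.00% | 8.25 | 1.85 |
| 10% / 20% | 20% / 5% | 8.98% / 19.51% | 10.53 | 2.17 |
| 15% / 15% | 5% / 20% | 14.63% / 13.48% | −1.15 | 0.92 |
| 15% / 15% | 20% / 5% | 13.48% / 14.63% | 1.15 | 1.085 |

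Equal stopping lowers the counts and shrinks the difference slightly, but leaves the ratio about unchanged. Unequal stopping moves the ratio towards less apparent harm from vitamins when that arm stops more, and towards more apparent harm when placebo stops more.

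The model is simple. It lets stopping begin at day 0, although in-hospital events are recorded on any reading, which overstates the loss a little. If patients who stop have more later events than others, the loss within that arm would be larger than shown.

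**The case against.** The strongest reply is that the sentence does not mean what the literal reading takes from it. The oral phase and the CMR follow-up both run 84 days, so naming oral treatment may simply be a way of naming the outpatient phase, as opposed to the hospital stay. The sentence covers all events, does not use the word only, and states no rule that recording ends at a stop. The statement under Randomization and followup has no time limit. A condensed article may also leave follow-up after discontinuation to the full protocol.

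Part of this stands. The shorthand reading is possible, so the article cannot be said to exclude these patients from safety collection. But the sentence is a stated rule, not an omission, and it is worded by treatment status in the same section that separates treatment from trial. Two sites could follow it differently in good faith.

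A reader might infer more, and the document does not support it:

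- **That patients often stop because of an event.** No reasons for stopping are given. An event that leads to a stop occurs on treatment and would be recorded; only later events are at risk.
- **That the comparison is biased towards no harm.** That needs more stopping on vitamins. The placebos are described as indistinguishable, and nothing indicates which arm would stop more.
- **That a vitamin E mortality signal would be missed.** The Discussion describes that signal as long-term and the meta-analysis as not applicable to this study. Randomization and followup also promises reasons for losses, so a death before day 84 should surface there, though not necessarily as an adverse event.

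**Conclusion.** The point holds as a defect of wording. The only sentence that sets an adverse-event window makes it depend on oral treatment, although the protocol allows patients to stop treatment and remain in the trial to day 84. Followed literally, it understates event counts in any arm with early stops. If stopping is unequal, it distorts the arm comparison in a direction that cannot be known in advance.

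Under assumed stopping of 5% in one arm and 20% in the other, a true risk ratio of 2.00 is recorded as 1.85 or 2.17. A true ratio of 1.00 is recorded as 0.92 or 1.085. These shifts are modest and rest entirely on assumed rates, independent stopping and the literal reading. If sites already follow everyone to day 84, there is no effect. This is a cheap improvement, not a threat to the primary analysis.

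**What to change.** Replace the window in Trial management with a calendar-based one, for example: *All adverse events and serious adverse events, including death and readmission, are collected from the first study dose to day 84 in every randomised patient who received any study treatment, whether or not oral treatment is started, continued or stopped.* Add that the weekly call continues for event collection after oral treatment stops, and that events since the last contact are asked about at the day-84 visit. In Statistical analyses, state that adverse-event frequencies are compared over this common window.

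The cost is one or two sentences in an amendment and a few more calls to patients who have stopped. The weekly calls and the day-84 visit already exist.

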## Discussion

Given the unpredictable nature of AMI, it is not feasible to obtain a basal myocardial image of patients; however, this trial also does not include performing an “acute” imaging on admission before the PCA (again, for feasibility reasons), but rather relies on performing a CMR on the sixth day after AMI. In this context, it is impossible to distinguish reperfusion damage from ischemic damage in the same patient, based in a single “6-day after” cardiac image. It would be expected on an imaging comparison among groups that on the 6^th^ and 84^th^ days, the placebo group exhibits, on average, a greater infarct size compared with the supplemented group. Any significant reduction of infarct size in the supplemented group could be attributed only to a decrease of reperfusion damage, because full coronary ischemia would not allow the arrival of ascorbate to the postoccluded artery segment. However, it will be impossible to determine whether a significant decrease of infarct size corresponds to total or partial reduction reperfusion damage.

To the best of our knowledge, no published reports have assessed human populations with high vitamin C levels in AMI patients during the PCA procedure; therefore, it is more difficult to compare data obtained with those in the current literature. In addition, given the characteristics of the study population, trial results are not applicable to patients having a second AMI, III or IV Killip score AMI, or other conditions established in the trial-exclusion criteria. Given that this study is being performed in a mostly Chilean population, its applicability to other ethnicities is uncertain.

Concerning the loss of data or patients during the study, patients undergoing a claustrophobic reaction will not be capable of being analyzed by CMR. Furthermore, due to the ambulatory nature of the trial, a small loss of patients may occur between the day 6 CMR and day 84 CMR. Given the multicentric nature of the study, the loss of samples is possible.

To our knowledge, no previous attempts have been made to use high doses of ascorbate to prevent or attenuate the myocardial damage caused by AMI. Pharmacokinetic studies on vitamin C in humans have shown that short-term infusion of high doses makes possible the reaching of peak concentrations even higher than 20 m*M*, but never being below 10 m*M* for at least 3 hours [84]. High doses of intravenous vitamin C have been reported to be remarkably safe, even when administered by infusions at a rate 3 times higher than that here proposed [85]. Nevertheless, patients having renal impairment or glucose 6-phosphate dehydrogenase deficiency, known possible complications of intravenous vitamin C, will be excluded from the present trial. However, a theoretic risk derived from high vitamin C levels is the development of kidney stones in unreported or first-time stone-forming patients [85]**.**

Regarding vitamin E possible adverse effects, current epidemiologic evidence (based on clinical trials that tested the effect of vitamin E supplementation in healthy participants and patients with various diseases) found that long-term supplementation with this nutrient shows a trend toward increasing slightly all-cause mortality (RR, 1.03; 95% CI, 1.00 to 1.05) independent of dose and exposition time [86]. However, the confidence interval is barely significant, because the lower interval is 1.00. In addition, as the Cochrane Meta-analysis explicitly excludes tertiary prevention trials, that is, randomized studies in which antioxidant supplements were used to treat a specific disease, such as trials involving patients with acute conditions (except nonmelanoma skin cancer), their conclusions are not applicable to our study.

Concerning the dosage, a previous meta-analysis reported that high-dosage supplementations (doses ≥400 IU/d) only increase all-cause mortality with expositions equal to or greater than 1 year [87]. Specifically in cardiovascular diseases, two recent meta-analysis that evaluate the efficacy of antioxidant supplements on these pathologies found no overall harmful effects in the analyzed endpoints [88,89], with the only exception of one controlled clinical trial [90]. However, those results are not consistent with the other related long-term large controlled clinical trials. In any case, that study supplemented the patients with twice our dose for more than a year, not being comparable in dose and timings with our study.

This novel strategy, by using innocuous and easily available substances, might significantly improve the clinical outcome of AMI patients, by reducing the infarct size, otherwise likely to result in working disability and diminution of both their life quality and expectancy.

Given the high incidence of AMI throughout the world and the innocuous and easily available substances used in the study, large-scale replication of this clinical trial worldwide seems feasible to the authors.

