### Study population

Patients of either sex, older than18 years, with an indication for primary percutaneous coronary angioplasty and experiencing their first acute myocardial infarction, admitted to University of Chile Clinical Hospital or San Borja Arriarán Clinical Hospital, will be invited to participate in the study. Inclusion and exclusion criteria are expressed in Tables 1 and 2, respectively.

**Table 1 T1:** Inclusion criteria of the study protocol

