**Exclusion criteria**	
1	History of renal or hepatic insufficiency
2	History of renal lithiasis
3	History of heart failure (New York Heart Association III, IV)
4	Cardiogenic shock
5	Postprimary PCA TIMI grade flow of 0, 1, or 2
6	Any serious medical comorbidity that determines life expectancy <6 months
7	Current participation in any other clinical investigation
8	Pregnancy
9	Glucose 6-phosphate dehydrogenase deficiency

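### Table 2 does not exclude Killip III failure at admission, although the Discussion places it outside the trial; either infusion would give such a patient 960 ml and about 307 mmol sodium in 3 hours

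*Protocol article*

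**What the plan says.** The protocol article describes the population in two places.

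- **Study population.** "Inclusion and exclusion criteria are expressed in Tables 1 and 2, respectively". Both tables are itemised. Table 1 requires a first infarction. The two cardiac-failure items in Table 2 are item 3, "History of heart failure (New York Heart Association III, IV"), and item 4, "Cardiogenic shock".
- **Discussion, paragraph on applicability.** Reasoning from the characteristics of the study population, it says the results will not carry over to patients with a second infarction, "III or IV Killip score AMI, or other conditions established in the trial-exclusion criteria".

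The Interventions section sets the infusion. Sodium ascorbate at 320 mM is "infused at a 10-ml/min flow rate during the initial hour and at 3 ml/min rate during the following 2 hours". It starts once consent is signed, and "Percutaneous coronary angioplasty will be performed about 30 minutes after initiating the vitamin C infusion". In the control arm it is "replaced by an equal sodium chloride solution volume having the same osmolality as the vitamin C infusion".

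The safety paragraphs of the Discussion link exclusions to renal impairment and G6PD deficiency, "known possible complications of intravenous vitamin C, will be excluded from the present trial". They do not discuss the volume or the sodium content of the infusion.

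**The concern.** The Discussion and Table 2 describe different populations. In the Discussion sentence, second infarction corresponds to Table 1 item 4 and Killip IV to the cardiogenic shock item. The word *other* before the remaining exclusion criteria implies that Killip III is a criterion too, yet neither table contains it. A site applying the tables would accept a patient whom the Discussion treats as outside the trial.

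The gap matters because of what is infused. A patient already in acute failure from a first infarct could receive a rapid volume and sodium load in either arm, part of it before the artery is opened. In the control arm there is no active treatment to set against that load. The trial could also enrol patients to whom, by its own statement, the results do not apply. The load is about the same in both arms, so nothing is claimed about the between-arm difference.

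**Working it through.** The article states neither the total volume nor the sodium load, so there is no figure of its own to reproduce.

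**Step 1: does any criterion catch Killip III at admission?** The article does not define the Killip classes. I use the standard meaning: III is acute pulmonary oedema and IV is cardiogenic shock.

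| Condition in the Discussion sentence | Matching criterion |
|---|---|
| Second infarction | Table 1 item 4 |
| Killip IV | Table 2 item 4 |
| Killip III | None. Table 2 item 3 concerns prior failure, not new failure at presentation |

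The TIMI-flow criteria do not help. They say nothing about failure, and they are known only at angiography or after the procedure, when the infusion is already running.

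**Step 2: the load in the vitamin arm.** Inputs from Interventions: 320 mmol/L sodium ascorbate (one sodium per ascorbate), 10 ml/min for 60 minutes, then 3 ml/min for 120 minutes, with angioplasty about 30 minutes after the start. Sodium = volume × 320 mmol/L; the mass uses 22.99 g/mol.

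| Period | Volume | Sodium |
|---|---|---|
| Before angioplasty (30 min) | 10 × 30 = 300 ml | 0.300 × 320 = 96 mmol (2.2 g) |
| First hour | 10 × 60 = 600 ml | 0.600 × 320 = 192 mmol (4.4 g) |
| Whole infusion (3 h) | 600 + 3 × 120 = 960 ml | 0.960 × 320 = 307.2 mmol (7.1 g) |

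For scale, 0.9% saline contains 9 / 58.44 = 0.154 mol/L sodium, and 307.2 / 154 = 1.99 litres. This equates sodium only; the infused volume is 960 ml.

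**Step 3: the load in the placebo arm.** With full dissociation, 320 mM sodium ascorbate is 2 × 320 = 640 mOsm/L. Sodium chloride of the same osmolality is 640 / 2 = 320 mM, so 960 ml again carries about 307 mmol. With an assumed osmotic coefficient of 0.93 for sodium chloride and 0.90 to 1.00 for ascorbate, the range is 307.2 × 0.90 / 0.93 = 297 mmol to 307.2 × 1.00 / 0.93 = 330 mmol.

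**Step 4: recruitment still open.** Trial status reports 43 enrolled. Against the 134 in the Abstract, 134 − 43 = 91 remain (68%). Against 66 per arm in Sample size, 132 − 43 = 89 remain (67%). The Killip III share is not in the article. On an assumed 1% to 5%, between 0.01 × 89 = 0.9 and 0.05 × 91 = 4.6 patients, about 1 to 5, would be affected.

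**The case against.** The strongest reply is that the Discussion shows the investigators already regard Killip III as excluded, and that Table 2 merely expresses this poorly through its NYHA and shock items. The full protocol and screening form are not shown, and nothing shows that such a patient has been enrolled. That is a fair reading of intent. It does not change the rule as printed: the article says the criteria are in the two tables and itemises them, and a site can apply only what they contain. If exclusion is the intent, adding the item only puts it into effect.

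A second reply is that the hazard is a clinical inference. The article sets no volume or sodium limit and reports no fluid-related harm. It also describes high-dose intravenous vitamin C as safe at three times the proposed rate, excludes renal insufficiency, prior NYHA III–IV failure and shock, and provides for safety withdrawal and prompt reporting of adverse events to the chief investigator. These protections are real but partial. The people behind the infusion-rate statement are not described, and the same part of the Discussion says the authors know of no previous use of high-dose ascorbate against myocardial damage from infarction, so the statement cannot be carried over to acute failure. Withdrawal and adverse-event reporting act only after exposure.

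It is also true that few patients are likely to be affected and that their number is assumed. That bears on how much weight the point carries, not on whether it is correct.

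**Conclusion.** The concern holds. The Discussion and Table 2 contradict each other on Killip III, and under the tables as printed a first-infarct patient in new Killip III failure can be randomised. That patient would receive 960 ml and about 307 mmol sodium within 3 hours in either arm, with about 300 ml and 96 mmol before angioplasty.

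The conclusion rests on the standard Killip definitions and, for the placebo arm, on inferring sodium from matched osmolality. That excess volume and sodium are undesirable in acute pulmonary congestion is a clinical judgement, which the article does not address. The number of patients exposed is unknown. This should be corrected while about two thirds of recruitment remains; it does not threaten the validity of the treatment comparison.

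**What to change.** Add *Killip class III or IV at admission* to Table 2 for the remaining recruitment, and report Killip class at entry for patients already enrolled, where it was recorded. If the investigators do mean to include Killip III, they should instead delete it from the Discussion sentence and justify the volume and sodium load for those patients in both arms.

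The cost is a one-line amendment with ethics notification and slightly fewer eligible patients. On the assumed 1% to 5% share, about 1 to 5 of the remaining 89 to 91 places would be filled by other patients.
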